**Discussion:**

The SuperB trial is a multicentre randomized controlled trial designed to show non-inferiority in patency rates of the heparin-bonded endograft compared to the surgical bypass for treatment of long SFA lesions, and to prove a better quality of life using the heparin bonded-endograft compared to surgically treatment, related to a reduction in complications.

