### Study objectives

The aim of the study is to demonstrate that the heparin-bonded endograft provides equal patency rates compared to the venous surgical femoro-popliteal bypass. In addition we hypothesize that patients receiving a heparin-bonded endograft show better quality of life at 30-days compared to patients who were surgically treated.

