### Sample size calculation

The assumption has been made that the heparin-bonded endoluminal bypass will have a similar cumulative primary patency at one year compared to the venous bypass. For a non-inferiority trial with an effect size of 90% and a margin of 10%, 111 patients per group are needed (alpha 5%, power 80%). The effect size of 90% refers to an estimated patency rate at one year in the surgical control arm.

The assumption has been made that the heparin-bonded endoluminal bypass will have an increase in QOL, as measured by a 10-point increase in the SF-36 score, at 30 days follow-up. With a standard deviation of 20, 63 patients per group are needed (alpha 5%, power 80%).

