### Primary endpoints

The primary endpoints of the study are the primary patency at 1-year follow-up. In addition the quality of life, using the RAND SF36 Questionnaire will be evaluated as a primary endpoint.

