### Statistical analyses

Data concerning the 1, 2, and 5 year follow-up will be analyzed for both study groups on an intention-to-treat and a per-protocol manner by student t-test (normal distribution) of Mann Whitney U-test (skewed distribution). Corrections will be made for study centre. Additionally, in case of sufficient numbers, the data will be analyzed for different TASC II categories; otherwise the analyses will be additionally adjusted for TASC II categories. Patency rates will be presented as Kaplan Meier curves including censoring.

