### Definitions

• Procedural success:

○ Endovascular - Successful vascular access, exact deployment of the device and completion of the endovascular procedure and immediate morphological effect (< 30% residual stenosis)

○ Surgical - Successful access, completion of surgical procedure and clinically assessed immediate improvement

• Primary patency: The absence of occlusion or flow-limiting stenosis (PSV ratio > 2.5) of the treated segment of the artery including 1 cm proximal and distal of the anastomosis, as documented by accepted imaging techniques, particularly arteriography or duplex ultrasonography, or direct observation at operation or postmortem.

• Primary assisted patency: When a secondary endovascular or open procedure is performed to prevent failure, i.e. in a flow reducing stenosis (PSV ratio > 2.5), in a still-patent segment of the stent graft or bypass, including the anastomoses.

• Secondary patency: When a thrombolytic or surgical treatment has been performed for graft or stent graft occlusion in an afterwards patent vessel.

• Target lesion revascularization: Repeat percutaneous or surgical revascularization driven by clinical state in the presence of a flow reducing stenosis or occlusion in the treated segment of the artery including 1 cm proximal and distal of the anastomosis.

• Type B lesion SFA according to TASC II criteria:

○ Multiple lesions (stenosis or occlusions), each ≤ 5 cm

○ Single stenosis or occlusions ≤ 15 cm (not involving infragenuale popliteal segment)

○ Heavily calcified occlusion ≤ 5 cm in length

○ Single popliteal stenosis

• Type C lesion SFA according to TASC II criteria:

○ Multiple stenosis or occlusions totaling > 15 cm with or without heavy calcification

○ Recurrent stenosis or occlusions that need treatment after 2 endovascular interventions

• Type D lesion SFA according to TASC II criteria:

○ Chronic total occlusions of CFA or SFA (> 20 cm, involving the popliteal artery)

○ Chronic total occlusions of popliteal artery and proximal trifurcation arteries

• Minor amputation: Below the ankle amputation, planned or unplanned.

• Major amputation: Above the ankle amputation, planned or unplanned

• Clinical improvement: Improved Rutherford classification compared to baseline.

• Intermediate lesion: Occlusion or stenosis > 10 cm length

• Flow-reducing (re-)stenosis: A stenosis with a PSV ratio of more than 2.5 as measured by duplex, or a > 50% (re-)stenosis on angiography, MRA or CTA.

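### No stated analysis tests the 10% non-inferiority margin on 1-year primary patency: the only named tests are zero-difference t or Mann-Whitney tests

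*Protocol article*

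**What the plan says.** All places are in the protocol article.

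- **Hypothesis.** The Discussion paragraph of the Abstract describes the trial as "designed to show non-inferiority in patency rates of the heparin-bonded endograft compared to the surgical bypass".
- **Endpoint.** Primary endpoints: "The primary endpoints of the study are the primary patency at 1-year follow-up". Quality of life is named as a further primary endpoint. Definitions gives "Primary patency: The absence of occlusion or flow-limiting stenosis (PSV ratio > 2.5) of the treated segment of the artery", so at any time a treated segment is either patent or not.
- **Sample size.** Sample size calculation: "For a non-inferiority trial with an effect size of 90% and a margin of 10%, 111 patients per group are needed", with alpha 5% and power 80%. The 90% is the expected 1-year patency in the surgical arm, and the two arms are assumed to be similar.
- **Analysis.** Statistical analyses is the only analysis text. It sends the data of the 1-, 2- and 5-year follow-up, without restricting them to particular outcomes, to analysis "on an intention-to-treat and a per-protocol manner by student t-test (normal distribution) of Mann Whitney U-test (skewed distribution". It adds that centre will be corrected for, and that "Patency rates will be presented as Kaplan Meier curves including censoring".
- **Aim as worded.** Study objectives sets out to "demonstrate that the heparin-bonded endograft provides equal patency rates compared to the venous surgical femoro-popliteal bypass". The Background paragraph of the Abstract and the Discussion also speak of equal patency or equality.

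**The concern.** The trial is sized on a margin, yet the margin does not return in the analysis. A Student t-test or Mann-Whitney test, as named, asks whether two groups differ from zero. Neither accommodates censored follow-up, which the same section expects for patency. The choice between them by normal or skewed distribution has no meaning for a patent/not-patent outcome. The Kaplan-Meier curves are to be presented; no confidence bound, comparison with 10% or decision rule goes with them.

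The years named in that sentence are the ones at which Study design places primary patency, so a reader would take the sentence to include the primary endpoint. What is at stake is the main conclusion of the trial. Failing to find a difference does not show that the endograft is not worse by more than the margin, and a smaller or noisier trial fails to find a difference more easily.

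**Working it through.** **1. Reproduce the stated sample size.** Inputs from Sample size calculation: patency 0.90 in both arms, margin 0.10, alpha 5%, power 80%. For a non-inferiority comparison of two proportions,

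n per group = [p1(1−p1) + p2(1−p2)] × (z_alpha + z_power)² / margin²

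With one-sided 5%: 0.18 × (1.645 + 0.842)² / 0.01 = 111.3. This agrees with the stated 111 apart from rounding. Other readings do not reproduce it:
- one-sided 2.5% gives 142;
- a relative margin (9 points) gives 138;
- a superiority test of 90% v 80% gives 199 two-sided or 157 one-sided.

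The 111 therefore rests on an absolute 10-point margin and a one-sided 5% non-inferiority test. The article states neither the sidedness nor that the margin is absolute; both are inferred from this match.

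**2. Power at 111 per group.** SE = √(0.18/111) = 0.0403 and 0.10/0.0403 = 2.483.
- One-sided 5%: Φ(2.483 − 1.645) = 79.9%.
- One-sided 2.5%: Φ(2.483 − 1.960) = 70.0%.

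**3. Zero-difference test when the truth lies on the margin (90% v 80%).** SE = √[(0.09 + 0.16)/111] = 0.0475, so the shift is 0.10/0.0475 = 2.11. The chance that a two-sided 5% test is non-significant is P(|Z| < 1.96) with that shift, about 0.44.

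**4. Exact enumeration.** Binomial outcomes with 111 per arm and every patient's 1-year status known. The margin rule is a Wald upper one-sided 95% bound for surgery minus endograft below 10 points.

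| True patency, surgery v endograft | t-test non-significant | Mann-Whitney non-significant | Margin rule met |
|---|---|---|---|
| 90% v 90% | 94.7% | 94.8% | 80.3% |
| 90% v 85% | 79.2% | 80.0% | 31.6% |
| 90% v 80% | 43.7% | 44.7% | 5.4% |
| 87% v 77% | 50.4% | 50.6% | 5.3% |
| 90% v 78% | 30.0% | 30.8% | 2.2% |

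The 87% is the 1-year patency that the article's Background gives for venous bypass. At 90% v 80% the ratio is 43.7/5.4, about 8.

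**5. One concrete result.** Suppose 100/111 v 92/111 are patent. The difference is 8/111 = 7.2 points, and either named test gives p = 0.12. SE = √[(0.901×0.099 + 0.829×0.171)/111] = 0.0456, so the upper one-sided 95% bound is 7.2 + 1.645 × 4.56 = 14.7 points. There is no significant difference, yet non-inferiority is not shown.

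**The case against.** The best defence is that the t-test sentence was never meant for patency. A choice by normal or skewed distribution suits continuous outcomes. Follow-up has quality-of-life scores and ankle-brachial indices measured at all visits, so continuous data exist at 1, 2 and 5 years. Patency has its own Kaplan-Meier sentence. What is then absent is a formal decision rule, which an article may leave to the full protocol or analysis plan.

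This reading is possible, but the sentence covers the follow-up data without qualification, and even on this reading patency is only displayed. Either way the section needs to say which outcomes the two tests cover and how patency meets the margin.

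Other parts of the defence stand and limit the point:
- A reader might infer that the investigators will take a non-significant p-value as equal patency. The article does not say so. Non-inferiority is stated in the Abstract, Sample size calculation and Discussion, and the margin in the first two of these. The wording about equality only leaves that misreading open.
- A reader might infer that the named tests are incapable of addressing the margin. That is too strong: a t-based confidence interval on 0/1 data could be compared with 10 points. The article does not propose this, and Mann-Whitney offers no direct comparison with a 10-point margin.
- The promised correction for centre suggests some method beyond the bare tests, and both tests have extensions that allow it. Centre is therefore not counted against the plan.
- The conditional handling of TASC II categories covers both cases and is a matter of preference, not part of this point.

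**Conclusion.** The point holds in this form: followed as written, the Statistical analyses section contains no analysis that tests the non-inferiority hypothesis on which the trial is sized. That is a mismatch between stated parts of the plan and goes beyond omitted detail. It falls on a primary endpoint.

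The size is conditional. About 44% against about 5% at 90% v 80% (50% against 5% at 87% v 77%) describes a rule that treats non-significance as success. The article does not state that rule, so these are not the error rates of the plan itself. They assume 111 evaluable patients per arm, no censoring, a two-sided 5% zero-difference test, an absolute 10-point margin and a one-sided 5% non-inferiority level. The last two are inferred from reproducing 111.

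**What to change.** 1. Limit the t-test/Mann-Whitney sentence to continuous outcomes such as RAND-36 scores and ankle-brachial index.
2. For 1-year primary patency, state that the between-arm difference in Kaplan-Meier patency at 1 year (surgery minus endograft) will be estimated with a confidence bound. Non-inferiority is concluded if the upper one-sided 95% bound is below 10 percentage points.
3. State the confidence level explicitly, because it decides the result. One-sided 95% is the level that gives 111 per group at about 80% power. If a one-sided 97.5% bound is preferred, say that power at 111 is about 70%; 142 per group would be needed for 80%.
4. Report the comparison in both the intention-to-treat and per-protocol sets already planned, and require both to agree.
5. Account for centre by a method that tolerates centres with no failures. At 90% patency about 11 failures are expected per arm (0.10 × 111), or about 2 per arm in each of the 5 centres if recruitment is even. Centre-by-centre Greenwood errors would then often be zero or unstable.
6. Replace the wording about equal patency or equality by non-inferior, meaning not worse by more than 10 percentage points.

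The cost is wording in the analysis section, the objectives and the matching sentences of the Abstract and Discussion. At the one-sided 95% level no extra patients or data are needed.

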### Secondary endpoints

1. Secondary patency

2. Complications

3. Clinical improvement

4. Surgical and endovascular re-interventions

5. Target lesion revascularization

Additionally an exploratory, thus hypothesis generating, subgroup-analysis will be performed.

- Patients with disabling intermittent claudication (Rutherford 3) will be analyzed separately using pain-free and maximal walking distance and the Walking Impairment Questionnaire as additional endpoints.

- Patients with ischemic rest pain and necrosis (Rutherford 4-6) will be analyzed using major amputations as an endpoint.

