### Inclusion criteria

· Patients over 18 years of age

· Informed consent

· De novo stenosis, re-stenosis (Peak Systolic Velocity (PSV) ratio > 2.5) or occlusion of the native SFA, all > 10 cm in length

· Popliteal artery is patent at the upper margin of the patella to the trifurcation

· Diameter of the native SFA and popliteal arteries are 5.0 to 7.5 mm

· Rutherford category 3-6

· Indication for surgical bypass

· Distal runoff at least 1 crural vessel without significant stenosis

· Resting ankle-brachial index (ABI) < 0.8 in the study limb prior to procedure

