### Randomization

Randomization will be performed during the out patient department visit in which the patient is included. The including physician will call the telephone number provided by the principle investigator. The person answering the phone will draw an envelope from a box of plain white envelopes containing the randomization choice. The envelopes are divided in batches of 20 and randomization is stratified by center.

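### Rutherford category (3 v 4-6), known at baseline for every patient, is in neither the stratification nor the stated adjustments; adding it would give a modest gain in precision and in protection against chance imbalance

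*Protocol article*

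**What the plan says.** Under Randomization, the only stratification factor is centre: "The envelopes are divided in batches of 20 and randomization is stratified by center".

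Under Statistical analyses, two adjustment variables are named. The first is unconditional: "Corrections will be made for study centre". The second is conditional: "in case of sufficient numbers, the data will be analyzed for different TASC II categories; otherwise the analyses will be additionally adjusted for TASC II". TASC II therefore enters as an adjustment only if the numbers do not allow analysis by category. As set out under Definitions, TASC II describes anatomy: lesion length, number, calcification and location.

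Rutherford category is known for every patient before treatment. It is an entry criterion ("Rutherford category 3-6") and the reference for a secondary endpoint ("Clinical improvement: Improved Rutherford classification compared to baseline"). Under Secondary endpoints it also splits the population for exploratory work: "Patients with disabling intermittent claudication (Rutherford 3) will be analyzed separately", with walking measures added, and "Patients with ischemic rest pain and necrosis (Rutherford 4-6) will be analyzed using major amputations as an endpoint". It is named neither as a stratification factor nor as an adjustment variable.

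**The concern.** The trial pools claudicants with patients who have rest pain or tissue loss, and the protocol regards the two groups as different enough to look at different outcomes in each. Clinical state may plausibly predict both primary endpoints, quality of life in particular. Because randomisation does not balance it, the share of category 4-6 can differ between arms by chance. Because the stated analysis does not adjust for it, any effect of that difference on the outcome stays in the estimate, apart from whatever centre or TASC II happens to absorb.

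At stake is the precision of both primary comparisons and how well the result of this single trial can be defended if the arms turn out unequal. If that happens, an adjustment fixed in advance is much easier to defend than one chosen afterwards.

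**Working it through.** **The plan's own figures (Sample size calculation).**
- Patency: 90% in both arms, margin 10 points, power 80%. n = 2 × 0.90 × 0.10 × (1.645 + 0.842)² / 0.10² = 111.3 per arm, against 111 stated. This matches when the 5% alpha is one-sided; one-sided 2.5% would need 142.
- Quality of life: difference 10, SD 20, two-sided 5%, power 80%. n = 2 × (1.96 + 0.842)² × 20² / 10² = 62.8, so 63, as stated.

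**Assumed inputs.** The documents do not give the share q of patients in category 4-6, or the outcome gap g between category 3 and categories 4-6. I take q = 20-50% and g = 5-20 points, on patency and on RAND-36 alike.

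**Formulas.**
- SD of the between-arm difference in q: √(2q(1−q)/111)
- 95% range of the shift in the treatment difference: ±1.96 × SD × g
- Share of outcome variance removed by adjustment: q(1−q)g²/0.09 for patency (0.09 = 0.90 × 0.10) and q(1−q)g²/400 for RAND-36 (400 = 20²)

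| q | SD of imbalance | 95% range of imbalance | Chance of ≥10 points | 95% shift, g = 5 / 10 / 20 | Patency variance removed | RAND-36 variance removed |
|---|---|---|---|---|---|---|
| 20% | 5.4 | ±10.5 | 6% | 0.5 / 1.1 / 2.1 | 0.4 / 1.8 / 7.1% | 1.0 / 4.0 / 16.0% |
| 35% | 6.4 | ±12.5 | 12% | 0.6 / 1.3 / 2.5 | 0.6 / 2.5 / 10.1% | 1.4 / 5.7 / 22.8% |
| 50% | 6.7 | ±13.2 | 14% | 0.7 / 1.3 / 2.6 | 0.7 / 2.8 / 11.1% | 1.6 / 6.3 / 25.0% |

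The bottom-right patency figure is a ceiling: with q = 50% and g = 20, an overall rate of 90% means 100% patency in category 3 and 80% in 4-6. For comparison, the standard error of the patency difference is √(2 × 0.09/111) = 4.0 points. At 63 per arm, the number planned for quality of life, the RAND-36 shifts are ±0.7 to ±3.5 points.

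**Power after adjustment (linear approximation).** Patency: from 79.9% to 80.1-83.9%. RAND-36 at 63 per arm: from 80.1% to 80.5-90.0%. The RAND-36 gain is stated before baseline score enters the model. Baseline score will carry part of the same information, so the additional gain from Rutherford will be smaller.

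**Validity without adjustment.** The unadjusted one-sided 5% non-inferiority test was simulated with 200,000 trials per scenario, for (q, g) = (35%, 10), (35%, 15) and (20%, 10).
- Over all trials, the mean estimate was −0.100 when the truth was −0.10. The error rate was 0.054-0.055, and power was about 0.80 when the arms were truly equal.
- The small excess over 0.05 does not come from omitting Rutherford. Each patient's category is drawn at random, so each arm's count is binomial at the overall rate whatever the gap; the excess belongs to the normal approximation.
- Among trials with an imbalance of 10 points or more (2.7-5.3% in each direction), the estimate moved by about 1.2-2.0 points. Power ranged from 0.64 to 0.92 and the error rate from 0.02 to 0.11, depending on direction and gap.

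**The case against.** The strongest reply is that nothing is broken. Randomisation makes the unadjusted estimate unbiased, its standard error already allows for chance imbalance, and the simulation bears this out. That stands. A reader might infer that an imbalance passes straight into the results and distorts the comparison. The documents do not support this: a shift needs both an imbalance and a prognostic effect, and no passage says how strongly Rutherford predicts either endpoint.

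Second, this is a journal article, and a fuller plan may list more covariates. That is fair, and it limits how hard the point can be pressed. But the article does not leave adjustment open: it names centre and TASC II, and a named set can be judged on what it includes.

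Third, TASC II is a reasonable choice for patency, which is an outcome of the treated segment. That also stands, and it is one reason to expect little from Rutherford there. It carries less weight for quality of life, where clinical state is the more natural predictor.

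Fourth, more covariates are not free when events are few. At 90% patency, 222 patients give about 22 failures (222 × 0.10). Crossing two Rutherford groups with five centres would leave about 11 patients per arm per cell (111/10). This stands and shapes the fix.

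A reader might also infer that Rutherford defines the only planned subgroups, or that its two groups are to be read on separate endpoints, so that patency and RAND-36 could never be compared between them. Neither holds. Statistical analyses also plans analyses by TASC II category. Under Secondary endpoints the claudicants' walking measures are described as additional, and nothing there excludes patency or RAND-36 from either group.

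**Conclusion.** The point holds as a modest improvement, not as a flaw that threatens the trial's conclusions. A baseline variable that every patient has, and that the protocol itself uses to divide the population, is missing from both the stratification and the stated adjustments.

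For patency, the likely shift is small against the 10-point margin: about a quarter of it at the 95% limit in the most extreme assumed case, and about 1.3 points at q = 35% and g = 10. The precision gain there is a few per cent of variance in most cases. The larger benefit is for RAND-36.

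All of these sizes rest on an assumed Rutherford mix and assumed outcome gaps, and they ignore any overlap with centre or TASC II. If Rutherford predicts the outcomes only weakly, the gain is close to nil. The statement that the comparison is unbiased applies to the intention-to-treat analysis.

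**What to change.** In Statistical analyses, add Rutherford 3 v 4-6, as recorded at randomisation, to the stated adjustments for both primary endpoints:

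- **1-year patency:** a two-stratum weighted risk difference, for example with Mantel-Haenszel weights, so that the 10-point margin stays on the scale on which it was set.
- **30-day RAND-36:** Rutherford group as a covariate alongside baseline score, which is already collected before the intervention.

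With about 22 expected patency failures, do not fully cross Rutherford with the five centres; state how the two are handled together, for instance as separate main effects. A treatment-by-Rutherford interaction is optional. If reported, it should be labelled exploratory, since so few failures give it very little power.

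The cost is a short addition to the analysis text. No new data are needed, and the sample size and randomisation procedure stay as they are.

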### Imaging

Ultrasound imaging screens all patients included in the study. Additionally, computed tomography angiography (CTA) or magnetic resonance angiography (MRA) will be performed. These imaging studies will be performed according to the local protocol of the participating centers. The lesions in the SFA will be categorized according to the Trans Atlantic Intersociety Consensus (TASC)-II criteria. Type B, C, and D lesions may be included.

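### TASC II adjustment of the overall comparison applies only when categories are too small for separate analysis; it should apply in every case

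*Protocol article*

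**What the plan says.** The Statistical analyses section of the protocol article names the comparison as "by student t-test (normal distribution) of Mann Whitney U-test (skewed distribution") and then adds, without condition, "Corrections will be made for study centre". Lesion type is handled by a two-branch rule. The first branch reads "in case of sufficient numbers, the data will be analyzed for different TASC II categories"; the second reads "otherwise the analyses will be additionally adjusted for TASC II categories".

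Three other places bear on this:

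- Imaging has every lesion graded by TASC II and says "Type B, C, and D lesions may be included", so there are three categories.
- Randomization says "The envelopes are divided in batches of 20 and randomization is stratified by center". TASC II is not a stratification factor, so its balance between arms is left to chance.
- Secondary endpoints declares the Rutherford subgroup analyses exploratory. The TASC II analyses carry no such label.

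**The concern.** The word joining the two branches makes them alternatives. If numbers are large enough, lesion type is examined category by category and nothing says the overall comparison is adjusted for it. If numbers are small, the overall comparison is adjusted. So the covariates in the main comparison depend on how recruitment falls across B, C and D.

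The two branches also answer different questions. Analysis by category asks what the effect is within each lesion type. Adjustment asks for one overall effect with lesion type taken into account. The first is no substitute for the second, and adjusting for three categories needs far fewer patients than analysing each alone. Wherever separate analysis is possible, adjustment is possible too, yet that is where the plan omits it. At stake are a primary model that is not fixed in advance and a little lost precision from a baseline variable already recorded.

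**Working it through.** **1. The plan's own sample size.** Inputs from Sample size calculation: control patency 90% at one year, margin 10%, alpha 5%, power 80%, and the endograft assumed to have the same patency. The sidedness of alpha is not stated. With one-sided 5%:

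n per group = 2 × 0.90 × 0.10 × (1.645 + 0.842)² / 0.10² = 111.3

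This matches the stated 111. One-sided 2.5% gives 142 and does not match. One-sided 5% is therefore used below.

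**2. Power of the by-category branch.** Assumption: an equal split, 111 / 3 = 37 per arm per category, with 90% patency in each. The documents give no shares.

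- Standard error = √(2 × 0.90 × 0.10 / 37) = 0.0697
- Margin / standard error = 0.10 / 0.0697 = 1.434
- Power at one-sided 5% = Φ(1.434 − 1.645) = Φ(−0.211) = 42%
- Power at one-sided 2.5% = Φ(1.434 − 1.960) = Φ(−0.526) = 30%

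**3. How far the branch depends on the cut-off.** With an assumed B/C/D split of 20/30/50%, the smallest category has about 0.20 × 111 = 22 per arm. In simulation, a required minimum of 15, 20 or 25 per arm in every category was met in about 94%, 54% and 7% of trials. Whether the overall comparison is adjusted can thus turn on a small change in the cut-off.

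**4. Effect on error and power.** 40,000 trials of 111 per arm were simulated per scenario. They compared a crude risk difference, a Mantel-Haenszel risk difference over the three TASC II strata, and the count rule (crude if every category reaches the minimum in both arms, otherwise adjusted; minimum 10 to 30). Type I error was taken with the endograft 10 points worse in every category, and power with no difference. Category patency rates and splits are assumptions.

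| Patency B/C/D; split | Power crude | Power adjusted | Gain (points) | Type I crude | Type I adjusted | Type I count rule |
|---|---|---|---|---|---|---|
| 93/90/87; equal | 80.5% | 80.7% | 0.2 | 5.6% | 5.8% | 5.6-5.7% |
| 93/90/87; 20/30/50 | 77.6% | 77.7% | 0.1 | 5.5% | 5.5% | 5.5% |
| 97/92/82; equal | 81.5% | 83.0% | 1.5 | 5.6% | 5.6% | 5.5-5.6% |
| 97/92/82; 20/30/50 | 74.8% | 75.9% | 1.1 | 5.2% | 5.3% | 5.2-5.3% |

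The small excess over 5% is present with crude analysis too, so the count rule does not cause it. Power in the 20/30/50 rows is lower mainly because average patency there is below 90% (for example 0.2 × 97 + 0.3 × 92 + 0.5 × 82 = 88.0%). Crude and adjusted conclusions differed in about 1-5% of trials. Centre was not simulated.

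**The case against.** The strongest defence has four parts.

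- **Order of preference.** Analysing separately when numbers allow, and adjusting otherwise, is coherent because separate analysis needs more patients. As a way of looking at lesion type this is fair. It does not explain why the overall comparison should lose its adjustment in the first branch.
- **A supplementary reading.** The sentence is introduced as an addition to the main comparison, so it may describe only extra analyses. The wording allows this, but it then leaves the role of TASC II in the main comparison unstated. The remedy is the same.
- **The missing threshold.** A minimum count, a merging rule and who decides are matters for a statistical analysis plan, which is not shown. This stands: the absent number alone is no finding. A threshold given elsewhere would still leave the either/or rule in place.
- **Small benefit.** This also stands; the gain is at most about 1.5 points.

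Two stronger readings are tempting. A reader might infer that lesion type is ignored when numbers suffice. The first branch says otherwise, since it then enters through the by-category analyses. A reader might also infer that the better of the crude and adjusted results may be kept once outcomes are known. In simulation that practice gave about 6.0-6.4% error at nominal 5%. The documents describe no such choice: the stated trigger is numbers, meaning counts of a baseline imaging grade. These are complete when recruitment ends, before the last recruited patients reach one year. The article does not say when the branch is chosen.

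**Conclusion.** The point holds as a minor one. As written, TASC II adjustment of the overall comparison is conditional on category counts and is not provided for when the categories are large. The main model is therefore not fixed in advance, and the by-category analyses offered in its place have about 42% power at one-sided 5%, assuming 37 per arm per category and 90% patency. There is no sign of error inflation from the rule itself, and the documents do not support a claim that results can be selected on outcome. The cost of leaving the rule alone is small: 0.1 to 1.5 power points across the four simulated scenarios, all resting on assumed shares and patency rates. The case for changing it is that a fixed model is cleaner and costs almost nothing.

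**What to change.** Replace the two-branch sentence with a fixed rule:

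- The overall comparison is adjusted for study centre and TASC II category in every case.
- A sparse TASC II category is merged with its neighbour under a count rule set before outcomes are seen.
- Results by TASC II category are reported as exploratory whatever the counts.

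The method must take covariates, which the plain t-test and Mann-Whitney U do not. For patency, a stratified risk difference is one example. Five centres by three categories make 15 cells, or 222 / 15 ≈ 15 patients per cell on average, so the weights and variance should be ones that remain valid in sparse strata.

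The cost is a revised analysis paragraph, a different primary method and slightly more analysis work. No new data are needed, because Imaging already requires the TASC II grade, and 111 per group stays as it is.
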